## Methods

2

The Kita Kneipp Study is a confirmatory, mixed-method, two-armed, waitlist, clinical, cluster RCT that was registered with the German Clinical Trial Register (DRKS-ID: DRKS00029275) on November 10, 2022 (submission for registration June 22, 2022), and approved by the Ethics Committee of the Charité - Universitätsmedizin Berlin (Application number: EA2/122/22, approved on September 13, 2022). It follows the standards of the Helsinki convention of good clinical practices.

This study protocol follows the SPIRIT (Standard Protocol Items: Recommendations for Interventional Trials) Guidelines for reporting study protocols (11).

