### Sample size

2.5

The sample size selection was formed by a preceding non-randomized controlled study (8) which focused on kindergarten sick days as a primary outcome. The study employed a Chi2-Test (categorizing kindergarten sick days as yes/no), revealing an effect size of *ω* (omega) = 0.41, equivalent to a Cohen’s *d* = 0.66 (8). Recognizing the non-randomized nature of the prior trial, the effect size was conservatively adjusted in half to φ (phi) = 0.205. With standard parameters set at *α* (alpha) = 0.05 (indicating a 5% probability of error in two-sided testing for differences), a power of 80% (*β* (beta) = 0.20), and accounting for an estimated dropout rate of approximately 20%, the optimal sample size for the current study was determined to be 240 child participants. The number of recruited matched kindergarten pairs will be based on the total calculated sample size.

Using a sampling strategy of maximum variation, semi-structured qualitative expert interviews will be planned with up to 15 kindergarten educators in the intervention facilities, while two focused ethnography observations will be each of the intervention kindergartens.

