### Recruitment, randomization, and assignment of intervention

2.6

Gate keepers at the Berlin governing structures responsible for kindergartens, contact leads from cooperative partners in Berlin will identify interested kindergartens. Members of the study team (SB – experienced scientific researcher, study coordination, AT – study administration) will contact these via email in which a flyer about the project will be included as additional information. Once interested, kindergartens will be contacted via telephone and site feasibility will be assessed for inclusion.

After being recruited to the study, kindergartens with a similar socio-economic level will be match-paired according to statistical demographic analysis of locations in Berlin (14).

The kindergartens will then be randomized within their matched pair to either the intervention or the waitlist group using the randomizing function of Python 3.10.6, executed by an experienced biostatistician (FK). The allocated study group will not be blinded, as this would not be possible due to the nature of the interventions. Therefore, the kindergartens, caregivers and children will be aware whether they are in the Kneipp or in the waitlist group.

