### Statistical methods

2.8

The study will be published in a peer-reviewed academic journal. Analyses of data will be performed after the collection is finalized according to the following hypotheses:

Primary Efficacy Hypothesis (Infection days leading to absence):Primary Null Hypothesis (H0): Implementation of a child-friendly Kneipp concept in the kindergartens does not lead to a significant reduction in infection-related absenteeism, after 12 months.Alternative Hypothesis (H1): Implementation of child-friendly Kneipp concept in the kindergartens results in a significant reduction in infection-related absenteeism, after 12 months.

Participant characteristics, stratified by groups (Kneipp vs. Control) will be presented. For continuous variables, descriptive statistics such as mean, standard deviation, and range will be calculated, while frequencies and percentages will be used for categorical variables.

The primary outcome will be the number of sick days reported to the kindergarten. To account for the expected overdispersion (right-skewed data because of high zero counts) in the count data, we will employ a negative binomial regression model. This model will include the group (Kneipp vs. Control) and the number of sick days at baseline as predictors. We will integrate unique kindergarten identifiers to determine if cluster effects exist.

For secondary outcome analysis, we will conduct an independent t-tests to compare the mean Common Cold Questionnaire (CCQ) scores between the Kneipp and Control groups. To investigate the interaction effects of group and sex, and group and age on CCQ scores, a two-way ANOVA will be performed. This model will include the main effects of group, sex, and age, as well as their interactions. If significant interactions are identified, post-hoc analyses will be conducted. Correlation analysis will involve calculating Spearman’s correlation coefficients to assess the relationships between CCQ scores and the number of sick days, and between CCQ scores and age. The correlation (ρ) will be interpreted based on conventional guidelines. To compare the frequencies of health outcomes such as colds, bronchitis, lung inflammation, antibiotic use, and gastrointestinal infections between the Kneipp and Control groups, chi-square tests will be performed. If the assumptions of the chi-square test are violated due to expected frequencies being less than 5, Fisher’s exact test will be used instead.

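### The primary model does not commit the test of group to account for kindergarten, the unit of randomisation, and gives the kindergarten identifiers only a checking purpose

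*Protocol article*

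**What the plan says.** The protocol article (Methods) calls the trial a "confirmatory, mixed-method, two-armed, waitlist, clinical, cluster RCT". Section 2.6 sets the unit and the restriction of allocation: "The kindergartens will then be randomized within their matched pair to either the intervention or the waitlist group". The matching is on socio-economic level of the location.

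Section 2.8 gives the primary analysis. For the count of sick days, "we will employ a negative binomial regression model". The predictors are listed: "This model will include the group (Kneipp vs. Control) and the number of sick days at baseline as predictors". The next sentence is the only one on clustering: "We will integrate unique kindergarten identifiers to determine if cluster effects exist". No term for the matched pair is named. Significance is declared at p < 0.05, and section 2.5 sets a two-sided alpha of 0.05.

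Section 2.5 gives no ICC and no number of kindergartens. It says that the number of pairs will follow from the total of 240 children.

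**The concern.** In a cluster-randomised trial, the variation between kindergartens is part of the error against which the group effect must be judged, whether or not a check detects it. The introduction itself notes that cross-infection is common in kindergartens, which is a reason to expect a positive ICC for illness absence.

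Section 2.8 gives the identifiers a diagnostic purpose and does not say how they enter the test of group. The reading matters:

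- **Check only.** Standard errors stay at child level and are too small.
- **Adjust only if the check is positive.** With few kindergartens the check often misses a real cluster effect, so the unadjusted test is used when it should not be.
- **Fixed predictors.** Group is constant within a kindergarten, so the group column equals the sum of the indicators of the intervention kindergartens. The group effect is not identifiable.
- **Random intercept, always kept.** This is sound in principle, but the text does not state it.

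At stake is the error rate of the one confirmatory test and the width of its confidence interval. A second, separate matter is that the pairs used in the allocation do not appear in the analysis.

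**Working it through.** **1. The plan's own figure.** Section 2.5 uses phi = 0.205, two-sided alpha 0.05, power 80% and about 20% dropout. For a chi-square test with 1 degree of freedom, N = (1.96 + 0.842)² / 0.205² = 186.8, so 187. Allowing for dropout, 187 / 0.8 = 234, close to the stated 240. The calculation therefore treats children as independent; no design effect enters. Analysed children: 240 × 0.8 = 192.

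**2. Assumed inputs.** The number of kindergartens K and the ICC are not in the document. I take K = 4 to 16 and ICC = 0.02 to 0.10. There is indirect support for K near 10. Section 2.3.1 plans interviews with the director and at least 2 other educators in every intervention facility, and section 2.5 allows up to 15 interviewees. If directors count among them, 15 / 3 = 5 intervention kindergartens, or 10 in all.

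**3. No adjustment.** With m = 192 / K children per kindergarten, the design effect is DE = 1 + (m − 1) × ICC, and the true two-sided error of a nominal 5% test is 2 × [1 − Φ(1.96 / √DE)]. For K = 10 and ICC 0.05: m = 19.2, DE = 1 + 18.2 × 0.05 = 1.91, 1.96 / 1.382 = 1.418, error = 15.6%.

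| K | ICC 0.02 | ICC 0.05 | ICC 0.10 |
|---|---|---|---|
| 4 | 15.9% | 28.4% | 41.2% |
| 8 | 10.5% | 18.1% | 28.1% |
| 10 | 9.3% | 15.6% | 24.3% |
| 16 | 7.6% | 11.5% | 17.6% |

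A negative binomial simulation (mean 3, dispersion 1, both assumed; 10 kindergartens of 19 children; 2,000 runs) agrees: 10%, 16% and 23%. Neither calculation includes the baseline covariate. A smaller simulation with it (800 runs, child-level correlation assumed) gave 9%, 12% and 18% if kindergarten differences persist from year to year, and 11%, 18% and 27% if they do not.

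**4. Adjustment only if the check is significant.** A Gaussian simulation under no effect (192 children, 20,000 runs per setting, no baseline covariate) gave, over ICC 0.02 to 0.10:

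- Matching explains nothing: 13–20% at K = 4, 8.5–11.6% at K = 8, 6.7–8.3% at K = 16.
- Matching explains half of the between-kindergarten variance: 5.8–6.8% at K = 8, 4.0–5.6% at K = 16.
- At K = 8 the check detects an ICC of 0.02, 0.05 and 0.10 in about 20%, 46% and 74% of runs.

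With no adjustment at all, informative matching reduces the excess but does not remove it: 8.0%, 11.6% and 18.1% at K = 8.

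**5. Random intercept always kept, Wald z-test, no pair.** With uninformative matching, 9.6–16.3% at K = 4 and 5.4–6.9% at K = 16. The excess comes from a normal reference with few clusters.

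**6. The pair.** An unpaired t-test on kindergarten means gave 4.8–5.2% when matching is uninformative and 2.4–4.0% when it explains half the variance. A paired analysis of kindergarten means gave 4.7–5.2% throughout. Leaving out the pair therefore never raised the error above about 5%.

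**7. Within-pair permutation.** With 5 pairs there are 2⁵ = 32 allocations, so the smallest two-sided p is 2 / 32 = 0.0625. With 6 pairs it is 2 / 64 = 0.031.

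**The case against.** The sentence on identifiers can be read charitably. Integrating them into the model could mean a random effect that is always kept. An article condenses a fuller plan, and an analysis plan not shown may settle random versus fixed effects, degrees of freedom and a fallback. Section 2.8 states no significance test for clustering and no rule for dropping the term, so the test-then-adjust scenario is one interpretation and not a stated procedure. The size of any inflation rests on an assumed ICC and K. All of this stands.

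It does not remove the point. The article does not leave clustering open: it lists the predictors and gives the identifiers a purpose, and that purpose is to find out whether an effect exists. The rest of the document fits a child-level reading: the sample size has no design effect, and the secondary group comparisons are ordinary t-tests, ANOVA and chi-square tests.

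Two stronger readings are tempting. A reader might infer that the primary p-value is certainly anti-conservative; the wording does not support that, because an always-kept random effect is possible and strong matching with many kindergartens can offset the excess under conditional adjustment. A reader might also infer that omitting the pair inflates type I error; step 6 shows that it leaves the error at about 5% or makes the test conservative.

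**Conclusion.** The concern holds as a failure to tie the confirmatory test to the unit of randomisation. If kindergarten is ignored, the error exceeds 5% for any positive ICC in the settings examined: about 9%, 16% and 24% for 10 kindergartens at ICC 0.02, 0.05 and 0.10, somewhat less if the baseline count absorbs lasting kindergarten differences. If adjustment depends on the check, the excess is smaller but remains in most settings. If the identifiers are fixed predictors, there is no estimate of the group effect.

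These figures rest on an assumed ICC and K, equal kindergarten sizes and, for step 4, a Gaussian approximation, so they indicate the order of magnitude for the planned model. The missing pair is a separate and lesser matter of power and fidelity to the design. The primary analysis sentence should be corrected, because a false-positive confirmatory result is at stake.

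**What to change.** Replace the sentence on identifiers in section 2.8 with a commitment along these lines: the primary negative binomial model includes group, baseline sick days and a random intercept for kindergarten that is kept whatever its estimate; inference on group uses a t reference with between-kindergarten degrees of freedom; the ICC is reported.

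Account for the matched pair in that model, or use a paired kindergarten-level analysis of baseline-adjusted rates, if the number of pairs leaves enough degrees of freedom. With 10 kindergartens, a comparison of means has 10 − 2 = 8 degrees of freedom unpaired and 5 − 1 = 4 paired, so the choice is a trade-off to make in advance. Use a within-pair permutation test only with at least 6 pairs.

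The cost is one or two sentences and no new data. The downside is wider intervals and some degrees of freedom spent on pairs.

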### Outcomes

2.4

The primary outcome measure is the number of absent days due to illness among 2-6-year-old children in randomized Berlin kindergartens for the Kneipp concept intervention kindergartens compared to the matched waitlist kindergartens over two time points (baseline prior to the intervention and 12 months after baseline).

Additionally, the CCQ (16) and the NCI-CTCAE Scales (17) describing gastroenterological-based symptoms will be used as a secondary outcome measure at each of the two timepoints as well. The study will also gather data on the number of days educators are absent due to sickness. This information will be subjected to statistical analysis as an additional secondary outcome measure, aiming to identify potential correlations between the absence of educators and that of the children.

Summarized findings will identify categories and themes from the qualitative content analysis of observations and interviews highlighting the practice and experiences of implementing Kneipp in the kindergarten and perceived changes.

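### The child-level t-test, ANOVA group effect and chi-square/Fisher tests for secondary outcomes ignore that kindergartens were randomised, so their p-values are probably too small

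*Protocol article*

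**What the plan says.** **Design.** Section 2.6 sets the unit of allocation: "The kindergartens will then be randomized within their matched pair to either the intervention or the waitlist group". Section 2.3 describes the same pairing and cluster randomisation.

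**Primary model.** Section 2.8 plans a negative binomial regression of sick days: "This model will include the group (Kneipp vs. Control) and the number of sick days at baseline as predictors". The next sentence brings in kindergarten identifiers, to see whether cluster effects exist. That sentence closes the paragraph on the primary outcome.

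**Secondary group comparisons.** The next paragraph of section 2.8 names three analyses:
- For CCQ: "we will conduct an independent t-tests to compare the mean Common Cold Questionnaire (CCQ) scores between the Kneipp and Control groups".
- For CCQ by sex and age, an ANOVA whose terms are listed: "This model will include the main effects of group, sex, and age, as well as their interactions".
- For five frequencies (colds, bronchitis, lung inflammation, antibiotics, gastrointestinal infection), compared "between the Kneipp and Control groups, chi-square tests will be performed". For small expected counts, "Fisher’s exact test will be used instead".

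No kindergarten, pair or baseline term appears in any of them. Section 2.4 says of CCQ and the NCI-CTCAE scales that they "will be used as a secondary outcome measure at each of the two timepoints as well", so baseline values will exist. Section 2.8 judges every analysis at p < 0.05.

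**The concern.** An independent-samples test takes each child as a separate piece of information about the group difference. Here the group was assigned to whole kindergartens, so anything that makes kindergartens differ (a local outbreak, attendance rules, staffing, neighbourhood) goes straight into the group contrast. The Introduction itself points to cross-infection among children and educators in kindergartens. Colds and gastrointestinal infections are therefore outcomes for which independence between children of one kindergarten is least plausible.

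The protocol recognises clustering for the primary outcome but then fixes secondary tests that leave it out. This is a named test that does not fit the design, not a detail left to an analysis plan. At stake are false-positive symptom and infection findings. In an open-label trial that calls itself confirmatory, these would be read as support for the primary result.

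**Working it through.** **1. The plan's own figure.** Section 2.5 gives φ = 0.205, two-sided α = 0.05, 80% power, about 20% dropout and a total of 240 children. For a one-degree-of-freedom chi-square test, N = (1.960 + 0.842)² / 0.205² = 187. Dividing by (1 − 0.20) gives 234, within 3% of 240. The figure is reproduced by a formula for independent children, with no design effect. I take 187 as the number analysed.

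**2. What the protocol does not give.** The number of kindergartens (section 2.5 lets the number of pairs follow from N), the children per kindergarten and the ICC. Assumed: 10 or 14 kindergartens, so m = 187/10 = 18.7 or 187/14 = 13.4; ICC ρ = 0.02, 0.05 or 0.10.

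**3. Error of a nominal 5% child-level test, no benefit from matching.** Design effect DE = 1 + (m − 1)ρ. Standard errors are understated by √DE. True type I error = 2[1 − Φ(1.96/√DE)].

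| Kindergartens | ρ | DE | √DE | True type I error |
|---|---|---|---|---|
| 10 | 0.02 | 1.35 | 1.16 | 9% |
| 10 | 0.05 | 1.89 | 1.37 | 15% |
| 10 | 0.10 | 2.77 | 1.66 | 24% |
| 14 | 0.02 | 1.25 | 1.12 | 8% |
| 14 | 0.05 | 1.62 | 1.27 | 12% |
| 14 | 0.10 | 2.24 | 1.50 | 19% |

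**4. Credit for matching.** If pairing removes a fraction f of the between-kindergarten variance from the arm difference, then DE = (1 − ρ) + mρ(1 − f). With 10 kindergartens and f = 0.5, DE is 1.17, 1.42 and 1.84 for the three ICCs, and the error is 7%, 10% and 15%. With f = 0.8, DE is 1.06, 1.14 and 1.27, and the error is 6%, 7% and 8%. The error returns to 5% only at f = 1 − 1/m, that is, when matching removes 93% (m = 13.4) to 95% (m = 18.7) of that variance.

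**5. Simulation.** With 192 children (240 less 20%), 12, 16 or 24 per kindergarten, ICC 0.02 to 0.10 and no pair effect (4,000 runs per setting):
- Independent t-test: 7.6% to 28.9%.
- Chi-square test: 6.5% to 21.9%. The ICC was set on the latent scale, so the binary tests are less inflated at the same nominal ICC.
- Group-by-sex interaction: 4.4% to 5.3%, so not inflated when the sex effect does not vary between kindergartens. Group-by-age was not simulated; age also varies within kindergartens.
- t-test on kindergarten means: 4.6% to 5.1%.

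**6. Baseline.** With correlation r between baseline and follow-up, adjustment multiplies the child-level residual variance by 1 − r²: 0.91 for r = 0.3 and 0.75 for r = 0.5. Both values of r are assumptions. The factor applies to child-level variance, not to the whole variance of the group contrast.

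**The case against.** **Scope.** A reader might infer that every secondary p-value is too small. The documents do not support that. The ANOVA is there mainly for its interactions, which compare children largely within the same kindergartens; only its group main effect is exposed. The Spearman correlations are not group comparisons. Educator sick days are a secondary outcome without a named group test. This part of the objection stands.

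**Size.** The number of kindergartens and the ICC are assumed, and the usual design effect gives no credit for pairing on socio-demographic data. That stands too: 8% to 24% is the case in which matching does not help. How well area-level matching predicts infection is unknown, and it would have to remove nearly all between-kindergarten variance to repair the tests.

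**Baseline.** A reader might also infer that leaving out baseline is a second validity error, because a pre-existing difference between kindergartens could pass for an effect. Under randomisation, a test that handles clusters correctly already allows for chance imbalance, so that argument restates the clustering problem. What remains is lost precision of unknown size. The text also does not say whether the CCQ t-test uses follow-up or change scores.

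**Could another sentence rescue the tests?** The kindergarten identifiers belong to the primary model. The remark in section 2.7 about aggregated anonymous data is too vague to mean kindergarten-level analysis, and tests by a child's sex and age imply child-level data.

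**Conclusion.** The point holds for three things: the CCQ t-test, the group main effect in the ANOVA, and the chi-square/Fisher comparisons. As written they do not fit a trial randomised by kindergarten. Their p-values are too small whenever paired kindergartens still differ more than trivially. Under the assumptions in steps 2 and 3 of the working, the true error of a nominal 5% test is about 8% to 24%. It falls to about 7% to 15% with 10 kindergartens if matching removes half the between-kindergarten variance. The direction is firm; the size rests on quantities that the protocol does not give.

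A reader might go further and conclude that the trial's main result is compromised by this. It is not: the primary model has its own baseline term and reference to kindergarten identifiers. Because only secondary outcomes are affected, this is a should-fix.

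**What to change.** Reword the secondary-outcome paragraph of section 2.8.

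- **CCQ.** Replace the t-test and ANOVA with a linear mixed model for follow-up CCQ with group, baseline CCQ, pair and a random kindergarten intercept. Use small-sample degrees of freedom (Kenward-Roger or Satterthwaite). Add group-by-sex and group-by-age to the same model. The correction matters: a rough simulation of such a model (pair as fixed effect, no baseline term) with uncorrected Wald tests, at 10 or 14 kindergartens with about 250 runs per setting, still gave about 6% to 9%.
- **Binary outcomes.** Use a GEE with a small-sample correction, or a paired analysis of kindergarten-level proportions where events are rare.
- **Baseline.** Include the baseline value as a covariate wherever it is collected, and describe it as an efficiency measure.

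No new data are needed, since kindergarten identifiers, pairs and baseline values are already planned. The cost is a change of wording, somewhat more analysis work, wider intervals and few degrees of freedom: a paired kindergarten-level analysis of 5 to 7 pairs has 4 to 6.

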### Data collection and management

2.7

The study will be conducted with two-time measurement periods, each 6 weeks long, whereby caregivers will complete an online questionnaire via online survey based on the CCQ and the NCI-CTCAE Scales describing gastroenterological-based symptoms at the end of each week of the data collection period.

At the beginning of each measurement period, caregivers will be asked to complete an initial onboarding questionnaire containing socioeconomic background information about the family. The first measurement period will be planned in autumn 2022, followed by a second measurement in the autumn of 2023 (see Figure 3: Data Collection Flowchart).

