**Figure 3 fig3:**
[figure not shown]
Data collection flowchart.

All teachers and caregivers will be informed about the purpose and implementation of the data collection as part of the evaluation via printed information sheets. The educator’s and parent’s written consent to participate will be collected (on paper) by the kindergarten directors. The following data will be recorded: Name, gender, date of birth, email, telephone number. Consents will be filed in a project folder and stored in a lockable office belonging to the kindergarten directors. The folders will be periodically checked during site visits by the study team (SB, MG – medical doctoral student, study coordination).

Focused ethnographies will be planned with the kindergarten staff to ensure that visits coincide with planned interventions. Based on these visits, willing staff will be asked to participate in a separately scheduled expert interview. Interviews will be audio-recorded, auto-transcribed via f4x (audiotranskription.de), corrected and pseudonymized. Transcripts and observation protocols will be uploaded and analyzed on a single computer with the qualitative analysis software MAXQDA 24 (Release 24.2.0).

At the beginning of the study, the study coordinator (SB) will create an electronic folder with a pseudonym for each participating kindergarten on a secure server. Documentation files with the following data will be stored in this folder:

– Main target parameters (missed days because of an infection)– Secondary target parameters (CCQ)– Interview audio and transcripts– Interview and observation field notes.

All results will be analyzed through anonymous aggregated data (quantitative part) or with the use of pseudonyms (qualitative part).

All collected study data will be collected and handled conforming to the Berlin Data protection Law (Berliner Datenschutzgesetz – BlnDSG) and in adherence with the Declaration of Helsinki code of ethics. The files will be stored in their anonymized and/or pseudonymized form after completion of the study on a Charité server for 10 years. Within the electronic survey system (SoSci), the participants are encrypted using IDs and are therefore not identifiable. The study coordinator (SB) will store the encryption list and will keep it in a locked cabinet. Access to the collected data will be restricted to members of the study team (SB, AT, MG, MB, GS, SW).

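### Sections 2.4 and 2.8 disagree on the secondary outcomes: three undeclared outcomes are tested, and the declared NCI-CTCAE gastrointestinal scales are not named in the analysis

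*Protocol article*

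**What the plan says.** Section 2.4 names the secondary outcomes. Beside the CCQ, the NCI-CTCAE scales "describing gastroenterological-based symptoms will be used as a secondary outcome measure at each of the two timepoints as well". For educator absence it adds: "This information will be subjected to statistical analysis as an additional secondary outcome measure". The abstract gives the same set.

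Section 2.7 describes two caregiver forms. Weekly, over 6 weeks in each of two periods, "caregivers will complete an online questionnaire via online survey based on the CCQ and the NCI-CTCAE Scales describing gastroenterological-based symptoms". At the start of each period, "caregivers will be asked to complete an initial onboarding questionnaire containing socioeconomic background information about the family". The abstract and section 2.1 add a third stream: absences and the reasons for them, from directors and, per the abstract, also from parents.

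In its secondary analysis paragraph, section 2.8 specifies a t-test, an ANOVA and correlations for CCQ scores. It then plans chi-square tests, with Fisher's exact test as the fallback, "To compare the frequencies of health outcomes such as colds, bronchitis, lung inflammation, antibiotic use, and gastrointestinal infections" by arm. The NCI-CTCAE scales are not mentioned in that section. A significance level of p < 0.05 applies to all analyses.

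**The concern.** A trial that calls itself confirmatory should test the outcomes it declares and declare the outcomes it tests. Here the two lists, a few pages apart in one article, differ in both directions. Bronchitis, lung inflammation and antibiotic use appear only in the analysis section. The gastrointestinal scales appear only in the outcome and data collection sections.

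The trial is open-label, and the Discussion itself warns of caregiver response bias. A significant difference in, say, antibiotic use could be reported beside the declared outcomes with nothing in the plan to tell a reader that it was never one of them. Conversely, a declared outcome collected on up to 12 weekly forms (6 in each of two periods) could be reduced to one yes/no comparison under a different name.

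**Working it through.** The plan gives no figure for this point. Its one design figure, 240 children, was set for the primary outcome and does not enter. The check is a mapping of outcomes to sources and tests.

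| Variable | Declared in 2.4 | Described source | Analysis in 2.8 |
|---|---|---|---|
| CCQ score | yes | weekly caregiver form | t-test, ANOVA, correlations |
| NCI-CTCAE gastrointestinal scales | yes | weekly caregiver form | not named |
| Educator sick days | yes | kindergarten record | no method named |
| Colds (frequency) | not as an event | plausibly the CCQ | chi-square or Fisher |
| Gastrointestinal infections (frequency) | not under that name | plausibly the NCI-CTCAE items | chi-square or Fisher |
| Bronchitis | no | reasons for absence at most | chi-square or Fisher |
| Lung inflammation | no | reasons for absence at most | chi-square or Fisher |
| Antibiotic use | no | none described | chi-square or Fisher |

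**Undeclared but tested.** Three of the five named comparisons. One of the three, antibiotic use, has no described source. A reason for absence is an illness or another cause, not a prescription. The other two could be read from the reasons for absence if diagnoses are entered there, but no diagnostic item is stated. That source would also miss a child who was ill and still attended, so the comparison would partly restate the primary outcome.

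**Declared but not named in the analysis.** The weekly gastrointestinal scales. The nearest test compares gastrointestinal infections as a frequency. A symptom grade reported weekly and a yes/no infection are different variables. The comparison also leaves out the first-period reports, although those are collected and the primary model does adjust for baseline.

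**Educator sick days.** Declared, but without a method in section 2.8. This is detail that an analysis plan may supply, so I do not count it as part of the point.

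**Stored-data list in section 2.7.** Its entry "Secondary target parameters (CCQ" names no other scale. It describes a documentation folder, not the set of endpoints, so it is weak evidence and the point does not need it.

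**Size of the multiplicity.** Inputs: level 0.05 per test (section 2.8), three undeclared outcomes, and the assumptions that each test holds its level, the tests are independent and no effect exists.

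1 - 0.95^3 = 1 - 0.857 = 0.143, or 14%.

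These outcomes probably occur together. With positive correlation the figure falls towards 5%, its value if all three tests gave the same answer. The range is therefore 5% to 14% for the three named outcomes. Because the list is introduced by 'such as', the number of tests has no stated upper limit.

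**The case against.** The strongest reply is that this is a condensed article. The weekly form is described only as based on two instruments, which is not an item list, and the data collection flowchart is not visible. A rule turning symptom grades into an infection is the kind of detail an analysis plan holds. All this stands, and it rules out several stronger readings that a reader might infer:

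- *No assessment could supply any of the three diagnosis and treatment items.* Not supported. Reasons for absence are collected and could hold bronchitis and lung inflammation. Only antibiotic use lacks any described source.
- *The gastrointestinal scales are collected and never analysed.* Not supported. The test on gastrointestinal infections is plausibly a use of those items.
- *The assessment schedules conflict.* Not supported. The abstract and sections 2.4 and 2.7 agree on two periods, and the abstract and section 2.7 on weekly reports over 6 weeks.
- *Diagnoses rest on long recall.* Not supported. No long recall period is stated, and the Discussion says weekly prompting is meant to limit recall for the CCQ.
- *The false-positive risk is 1 - 0.95^5 = 23%.* This assumes independence and counts colds and gastrointestinal infections, which do have a plausible source.

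The reply does not remove the disagreement between sections. An analysis plan can add a derivation rule. It cannot make an outcome tested in section 2.8 one that section 2.4 declares. It is also fair to say that the article states a single primary hypothesis, so these tests never carried confirmatory weight. They are nevertheless placed with the secondary outcome analyses and judged at the same threshold, which invites equal reading.

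**Conclusion.** The point holds as a mismatch between sections 2.4 and 2.8. Three of five frequency comparisons concern outcomes that section 2.4 does not declare. One of the three has no described source, and two depend on an unspecified record of reasons for absence. One declared outcome, the NCI-CTCAE gastrointestinal scales, is not named in the analysis and is represented at most by an unadjusted yes/no test. The chance of at least one spurious result among the three undeclared tests is between 5% and 14%, if each holds its level and they are not negatively correlated; an open list allows more.

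The conclusion rests on the article's own lists and not on what an unseen analysis plan may contain. It concerns secondary outcomes only. The primary hypothesis, the negative binomial model and the sample size of 240 are untouched.

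**What to change.** 1. In section 2.8, analyse the declared gastrointestinal outcome directly from the weekly NCI-CTCAE items: for example, the number of weeks with any symptom in the second period, adjusted for the same count in the first. If a gastrointestinal infection frequency is kept, say that it derives from these items.
2. Make sections 2.4 and 2.8 carry the same closed list of secondary outcomes, and drop 'such as'.
3. Restrict the frequency comparisons to items actually collected in the two 6-week periods, and state the source of each. If antibiotic use was not collected, remove it. If bronchitis and lung inflammation come from reasons for absence, say so.
4. Label the bronchitis, lung inflammation and antibiotic comparisons exploratory.

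The cost is wording in two sections and one model fitted to data already planned for collection. If data collection is complete, nothing needs to be collected again. The downside is that the diagnosis and antibiotic comparisons can no longer be presented as secondary outcome results.
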